| Office Manager                                | 7,681  | 9,643       | 12,169 | 10,607      | 19,850               | 20,249      | 40,100  | 19,850    | 20,249      | 40,100  |
| Co-I Assistant Scientist                      | 1,683  |             | 2,662  |             | 4,345                |             | 4,345   | 4,345     |             | 4,345   |
| Co-I Assistant Scientist                      | 1,363  |             | 2,151  |             | 3,514                |             | 3,514   | 3,514     |             | 3,514   |
| Liaison member                                | 25,635 |             | 42,298 |             | 67,933               |             | 67,933  | 67,933    |             | 67,933  |
| Co-I (RI-Training and Quality):               | 12,529 | 18,010      | 17,228 | 19,811      | 29,757               | 37,821      | 67,578  | 29,757    | 37,821      | 67,578  |
| Senior Master trainer                         | 20,659 |             | 25,565 |             | 46,224               |             | 46,224  | 46,224    |             | 46,224  |
| 2 Master trainer (Research Investigator)      | 23,299 | 28,164      | 35,239 | 30,980      | 58,538               | 59,144      | 117,682 | 58,538    | 59,144      | 117,682 |
| Senior Research Officers (Training & Quality) | 4,196  | 9,136       | 5,769  | 10,049      | 9,965                | 19,185      | 29,150  | 9,965     | 19,185      | 29,150  |
| Field Research Officers (Training & Quality)  | 10,073 | 4,871       | 18,467 | 5,358       | 28,539               | 10,229      | 38,768  | 28,539    | 10,229      | 38,768  |
| Field Research Officer                        | 5,036  |             | 1,847  |             | 6,883                |             | 6,883   | 6,883     |             | 6,883   |
| Field Research Assistant                      | 19,729 |             | 7,234  |             | 26,963               |             | 26,963  | 26,963    |             | 26,963  |

|                                                               |                |                |                |                |                |                |                  |                |                |                  |
|---------------------------------------------------------------|----------------|----------------|----------------|----------------|----------------|----------------|------------------|----------------|----------------|------------------|
| Bayley Tester (FRA)                                           | 6,576          |                | 6,028          |                | 12,605         |                | 12,605           | 12,605         |                | 12,605           |
| Senior Field Assistants                                       | 7,289          |                | 12,027         |                | 19,317         |                | 19,317           | 19,317         |                | 19,317           |
| Data management Supervisor                                    | 10,874         |                | 17,942         |                | 28,817         |                | 28,817           | 28,817         |                | 28,817           |
| Office/Field attendant                                        | 5,605          |                | 9,248          |                | 14,852         |                | 14,852           | 14,852         |                | 14,852           |
| Field Organizer (Office)                                      | 4,384          |                | 7,234          |                | 11,618         |                | 11,618           | 11,618         |                | 11,618           |
| Total 1.1 Remuneration - funding recipient's employees | 311,961 | 190,005 | 458,326 | 209,006 | 770,286 | 399,011 | 1,169,297 | 770,286 | 399,011 | 1,169,297 |

### Budget Justifications

Please provide one page statement justifying the budgeted amount for each major item, including the use of human resources, major equipment, and laboratory services.

**Personnel:** [name] is the project lead. She will dedicate almost 30% of her time to the implementation and full conduct of the project. [name]; the Co-PI of the project will spend 15% of her time. She will help in manual development and visiting Health officials, motivating their staff, analyzing data and drafting manuscripts. [name] will spend 30% of his time to help in implementing intervention and liaison with Govt. Stakeholders. [name], will develop the training curriculum for the Group Intervention and will also help in data analyses and manuscript writing. [name] will help in planning this scale-up project. She will provide advice on how to go forward and how to trouble-shoot. She will also help in data analyses and manuscript writing. Two Senior Research Investigators will work part time on this project and will be in charge of communicating with the GOB and maintaining a close liaison with the Ministries. There will be 3 master trainers (RIs), who will organize the trainings and observer and coach the health officers. In addition GCC requires Liaison member who will keep close contact with the GoB as well as GCC. The two research investigators will be in charge of test supervision and intervention implementation. There will be 1 senior Research Officer and 2 Research Officers responsible for trainings, quality control of intervention. In addition we need 6 junior facilitators who will be working at the field and keep track of all the stimulation activities as well as arrange logistics. We need 4 testers to perform Bayley test and anthropometry twice on 1200 children in the study. One data management supervisor is required for data entry and cleaning. Five Field Organizers are required to maintain liaison with CCs and are required to run errands like delivering letters to the ministries, collecting materials for tests, photocopying questionnaires, etc.

**Travel:** the PI will travel once every year to UK to discuss the plans with the 2 consultants in that country. The last trip will be to analyze the data and draft manuscripts. [name] will visit the field once during the preparatory phase and another time at the beginning of the intervention activities. Some local travelling expenses are required for the staff to move from one village to another and to bring the children for tests to the CCs. We will require some funds to prepare stimulation materials and for printing of books, manuals and questionnaires and arranging training workshops and launching and dissemination seminars. The equipments required are computers, printers, Bayley kits, and anthropometric tools.

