
## Description of the Research Project

### Hypothesis to be tested:

In a hypothesis testing research proposal, briefly mention the hypothesis to be tested and provide the scientific basis of the hypothesis, critically examining the observations leading to the formulation of the hypothesis.

Does this research proposal involve testing of hypothesis: ☐ No ☒ Yes (describe below)

We hypothesize that it is feasible to train GoB staff at District, Sub-district, Union and CC levels and integrate ECD activities in CCs in Bangladesh and thereby improve malnourished children's development after a year of intervention.

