### Specific Objectives:

Describe the specific objectives of the proposed study. State the specific parameters, gender aspects, biological functions, rates, and processes that will be assessed by specific methods.

General objective is to establish a sustainable programme whereby ECD activities are integrated into the routine activities of CCs in rural Bangladesh for undernourished children and national, district, sub-district, and union level trainers are developed to train clinic staff.

The specific objectives are:

1. To establish a mechanism for sustainability at central, district and sub-district levels: including training , supervision, monitoring and reporting
2. To assess the feasibility of the sustainable model including:
  - a) Coverage: Assess number of children participating in the programme

- b) *Compliance* of inspectors and clinic staff
  - i. Attendance at training,
  - ii. % of sessions run,
  - iii. % of sessions observed by inspectors
- c) *Fidelity*:
  - i. % of inspector reports correctly filled in
  - ii. % of sessions meeting acceptable standards
- 3. To assess the impact on maternal knowledge and depressive symptoms, stimulation in the home and child growth, cognition and language in a subsample

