### Sample Size Calculation and Outcome (Primary and Secondary) Variable(s)

Clearly mention your assumptions. List the power and precision desired. Describe the optimal conditions to attain the sample size. Justify the sample size that is deemed sufficient to achieve the specific aims.

**Sample size for the evaluation sample:** is calculated using a matched case-control design and effect size of 0.3 SD. We will select 10 children from 40 intervention and 40 control CCs. The control CCs will be the waitlisted CCs in the neighbouring districts of the same Divisions, where intervention has not started yet. The undernourished children will be identified by the research staff and asked to participate in the study. There will be 640 children required for the evaluation. We will add 25% to the sample size to account for losses during the study. Therefore, a sample of 800, 400 in each group will be sufficient to evaluate the study.

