### Outcome measures

1. Stimulation in the home measured by the Family care indicators (FCI)
2. Maternal knowledge of child rearing
3. Bayley Scales of Infant and Toddler Development-III: language and cognitive scales
4. Wolke's behaviour ratings of children during the Bayley test
5. Anthropometry (weight, length/height, head circumference)

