### Ethical Assurance for Protection of Human rights

Describe the justifications for conducting this research in human participants. If the study needs observations on sick individuals, provide sufficient reasons for using them. Indicate how participants' rights will be protected, and if there would be benefit or risk to each participants of the study. Discuss the ethical issues related to biomedical and social research for employing special procedures, such as invasive procedures in sick children, use of isotopes or any other hazardous materials, or social questionnaires relating to individual privacy. Discuss procedures safeguarding participants from injuries resulting from study procedures and/or interventions, whether physical, financial or social in nature. [Please see Guidelines]

Approval of the Research and Ethical Review Committees of icddr,b will be sought. This study will be associated with minimal risks. There are no known risks associated with play stimulation, cognitive and language testing or behavioural observations. Informed written consent will be obtained from the mothers of the participating children for stimulation and psychological examination. Purpose of the study, study procedures, requirements of participation, risks and benefits involved in participation and rights not to participate or withdraw from the study at anytime will be clearly explained. Mother will be invited to pre-set centres with the child for Bayley test and small snacks and travel cost will be provided. All information collected will be stored under lock and key and kept in a secure place under the close supervision of the Principle Investigator of this study. Data will be kept confidential. Consent papers will be signed in presence of a third person as a witness and one copy of the signed consent will be given to participant mother. The severely malnourished children and those who may be ill will be referred to nearby hospital or health centre through community clinics for further management.

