#### ২. Adaptability (slow vs quick to warm up) (অভিযোজন / পরিবর্তিত অবস্থায় নিজেকে মানিয়ে নেয়ার যোগ্যতা (ধীরগতি বনাম দ্রুততা)):

এই স্কেলটি নির্দেশ করে শিশু কত দ্রুত বা ধীরে দক্ষতার সাথে পরিস্থিতি এবং কাজ (নতুন খেলনা, জায়গা, বসা ইত্যাদি) এবং টেস্টারের সাথে খাপ খাওয়াতে পারে। (This scale refers to how quickly or slowly the infant adapts to the examination circumstances and procedures (new toys, place, sitting down, etc) and the examiner)

- ১। Constantly fearful; never trusting (Bayley-II), Infant remains withdrawn and timid ... (TRIB): শিশুটি টেস্টার পুরো অথবা বেশীর ভাগ সময়ই নির্বিকার বা ভীত থাকতে পারে। পরবর্তী কিছু অংশের টেস্টার সময় সংকোচ বোধ দেখাতে পারে। কেবল তখনই সামাজিক খেলায় সাড়া দিতে পারে কিন্তু আনন্দ পূর্ণ পারস্পারিক ক্রিয়া শুরু করে না। (Infant remains withdrawn and timid for all or most of the assessment, may show some signs of losing inhibition towards the later parts of the assessment, only then may respond to social play, but not initiating joyful interaction.)

- ২। ১ এবং ৩ এর মধ্যে। (Between 1 and 3)।

৩। Typically fearful; one or two instances of trust (Bayley-II): সাধারণত টেষ্টের ১টা অথবা ২টা অবস্থার উপর আস্থা রাখে অর্ধেক সময়ই নীরবকার, সারাক্ষণ ভীত এবং অপরিচিত টেষ্টারের প্রতি (Tester) বিরক্ত থাকে। ধীরে ধীরে ভয় কমে আসে এবং আনন্দপূর্ণ পারস্পারিক ক্রিয়া শুরু করে, শব্দ করার মাধ্যমে সামাজিক পারস্পারিক প্রতিক্রিয়া শুরু করতে পারে। টেষ্টের শেষের দিকে টেষ্টারকে খেলনা দিতে চাইতে পারে। (Remains withdrawn, timid and bothered by the stranger for about half of the assessment, slowly loses fear, and enters playful interaction, may also initiate social interaction by vocalising, offering toys to the examiner late through the assessment.

৪। ৩ এবং ৫ এর মধ্যে। (Between 3 and 5)।

৫। Fearful one third of the time; trusting the rest of the time (Bayley-II-modified): শিশুর ব্যবহার / আচরণ টেষ্টার দ্বারা প্রভাবিত হতে পারে, কিছু সতর্কতা থাকলেও শিশু টেষ্ট চলাকালীন অবস্থায় টেষ্টারকে প্রথম তৃতীয়াংশের সময়ের মধ্যে মেনে নেয় এবং ধীরে ধীরে সেটা শিথিল হয়ে যায়, পারস্পারিক প্রতিক্রিয়ায় সাড়া দেয়, মা এবং টেষ্টারের সাথে খেলতে শুরু করে। The behaviour is affected by the examiner there is some initial wariness but the infant accepts the assessment situation within the first third of the testing period, relaxes gradually during this first third, opens up to interaction, initiates play with examiner as well as mother.

৬। ৫ এবং ৭ এর মধ্যে। (Between 5 and 7)।

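### The protocol gives two test venues; end-of-study testing at the community clinics would let the place of testing differ by arm in a way the analysis cannot remove.

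*Protocol*

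**What the plan says.** Two places in the protocol bear on where children are tested. Under Ethical Assurance for Protection of Human rights: "Mother will be invited to pre-set centres with the child for Bayley test and small snacks and travel cost will be provided". Under Budget Justifications, Travel, local travel is justified partly as a means "to bring the children for tests to the CCs". The centres are not defined, and no other section fixes the venue.

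The rest of the design gives the venue its importance:
- **Delivery.** The general objective is that "ECD activities are integrated into the routine activities of CCs in rural Bangladesh".
- **Timing.** The hypothesis is that the programme will "improve malnourished children's development after a year of intervention".
- **Arms.** Arm is fixed by clinic: "The control CCs will be the waitlisted CCs in the neighbouring districts of the same Divisions, where intervention has not started yet".
- **Outcomes.** The Outcome measures section lists "Wolke's behaviour ratings of children during the Bayley test". In the appended Behaviour Rating Scale, Adaptability refers to "how quickly or slowly the infant adapts to the examination circumstances and procedures (new toys, place, sitting down, etc) and the examiner", and Exploration scores how far the child investigates objects and the surroundings, including the testing room as a new environment.

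**The concern.** At a CC that runs the programme, an intervention child sits the final test in a place already known from the sessions. A control child's clinic has held no sessions. Where a rating scores the response to a new place, part of the difference between arms could then reflect the room and not development. The examiner would also see which arm the child belongs to, both from the clinic itself and from the programme materials kept there, while making judgement-based ratings. Either effect would be read as an effect of the programme.

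**Working it through.** No figure in the protocol rests on the venue, so there is nothing to recompute. The check sets the statements side by side.

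**1. Do the two venue statements agree?** There are three readings.
- The centres are places other than CCs and the ethics section governs. The familiarity problem does not arise, and the budget clause is wrong.
- The centres are themselves CCs. The statements agree, and the problem applies in full.
- The budget clause governs. The problem applies in full.

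So the wording must be settled on any reading, and two of the three readings put the final test at the session site.

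**2. Is the venue aligned with arm?** Sessions run in the intervention CCs. Control CCs are waitlisted and have not started. The training content for clinic workers covers storing and maintaining toys and books at the CC, so programme materials are on the premises. Testing each child at the local CC therefore gives a programme setting in one arm only.

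**3. When does the difference arise?** Budget Justifications provides for two rounds of testing. Before the programme starts, neither arm has attended sessions, so familiarity from sessions can differ only at the final round. A baseline score does not contain it, and adjusting for baseline does not take it out.

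**4. Which outcomes can it reach?** The Behaviour Rating Scale has nine scales. Adaptability names the place among the circumstances the child adapts to, and Exploration scores investigation of the surroundings. That makes two of nine with a direct link to novelty of place. A link to Bayley scores through cooperation is possible, but it is an inference. Home stimulation, maternal knowledge and anthropometry are not plausibly changed by knowing the test room.

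**5. Can the planned analysis remove it?** Data Analysis proposes propensity score matching on baseline data about children, families and communities, plus multilevel modelling. Familiarity builds up after baseline, so it cannot enter the score. A rater's expectation is a property of the measurement and not of the child. A multilevel model allows for correlation within clusters, but it does not separate a shift shared by a whole arm from the effect of that arm.

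**6. Does the protocol protect against it elsewhere?** The methods, outcome and analysis sections say nothing about masking testers or about a neutral venue.

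**The case against.** The strongest reply is that there may be no contradiction. The centres are undefined and could be selected CCs, and the other statement is one clause in a travel budget that speaks of tests without naming the Bayley. The first part is fair, but it leaves the problem in place, because the session site is then the venue. The second part is weak: the same budget section gives the testers both the Bayley test and anthropometry, so the ordinary reading of tests covers both.

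A reader might infer more than the document supports:
- **That CC testing favours the intervention arm.** Direction is not settled. A child who knows the room may adapt faster yet explore less. Control children may also know their own CC, since CCs see children for illness and immunization.
- **That the Approach rating is affected in the same way.** As written, it rates the child's first reaction to the tester, not to the place.
- **That testers work by area, so that tester is confounded with arm.** No section says so. The protocol neither states it nor excludes it.
- **That a false-positive rate can be attached.** This needs a bias and an intracluster correlation, and the document gives neither.

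It is also fair to say that a neutral building does not mask the tester. The arms lie in different districts, so the locality can reveal the arm. That limits the remedy but does not remove the reason for it.

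Finally, the Project Summary makes coverage, compliance and fidelity the main outcomes, with child development assessed in addition in a subsample. This limits the reach of the point to that part of the evaluation.

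**Conclusion.** The point holds in this form. The venue statements must be reconciled. If final tests are held at CCs, arm-aligned familiarity and tester knowledge of arm can shift Adaptability and Exploration ratings, and possibly test cooperation, in a direction the document does not settle. The planned analyses cannot remove this.

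The size cannot be estimated from the protocol, and no number is offered. The conclusion rests on two things: that the final test is held at, or at a centre that is, a CC delivering the programme, and that intervention children have attended sessions there during the year. It does not rest on a session frequency. The fortnightly schedule in the Background section describes earlier trials.

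The change is worth making before testing starts, because the effect cannot be repaired afterwards and the correction is cheap.

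**What to change.** 1. In the Travel paragraph of Budget Justifications, change the destination for tests from the CCs to the pre-set centres.
2. In the ethics section, define those centres: the same type of venue in both arms and at both rounds, and none of them a CC delivering the programme.
3. Have each tester assess children from both arms within a Division. Record tester ID and include it in the outcome model. The model term can be placed in the statistical analysis plan.
4. Do not tell testers the allocation, and say plainly that full masking cannot be guaranteed because the arms lie in different districts.

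Cost: changes of wording and a tester schedule, with no extra staff. Travel cost for mothers is already promised. The downside is somewhat more travel for testers between neighbouring districts and for some families. Longer journeys could add to losses, so centres should be chosen with distance in mind.

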### Other Support

Describe sources, amount, duration, and grant number of all other research funding currently granted to PI or under consideration.

NA

|                             | Name of personnel/position                | Pay level | % Effort | # of posts | Monthly Rate | Year-1 | Year-2 | Year-3 | Year-4 | Year-5 | Total amount (US\$) |
| Payroll and Benefits:       |                                           |           |          |            |              |        |        |        |        |        |                     |
|                             |                                           |           |          |            |              |        |        |        |        |        |                     |
|                             |                                           |           |          |            |              |        |        |        |        |        |                     |
|                             |                                           |           |          |            |              |        |        |        |        |        |                     |
|                             |                                           |           |          |            |              |        |        |        |        |        |                     |
|                             |                                           |           |          |            |              |        |        |        |        |        |                     |
|                             | Sub-total of Payroll and benefits: |           |          |            |              |        |        |        |        |        |                     |
| Travel and transport        |                                           |           |          |            |              |        |        |        |        |        |                     |
|                             |                                           |           |          |            |              |        |        |        |        |        |                     |
|                             |                                           |           |          |            |              |        |        |        |        |        |                     |
|                             |                                           |           |          |            |              |        |        |        |        |        |                     |
|                             |                                           |           |          |            |              |        |        |        |        |        |                     |
|                             | Sub-total of Travel and Transport: |           |          |            |              |        |        |        |        |        |                     |
| Supply and materials        |                                           |           |          |            |              |        |        |        |        |        |                     |
|                             |                                           |           |          |            |              |        |        |        |        |        |                     |
|                             |                                           |           |          |            |              |        |        |        |        |        |                     |
|                             |                                           |           |          |            |              |        |        |        |        |        |                     |
|                             |                                           |           |          |            |              |        |        |        |        |        |                     |
|                             | Sub-total of supply and materials: |           |          |            |              |        |        |        |        |        |                     |
| Other contractual           |                                           |           |          |            |              |        |        |        |        |        |                     |
|                             |                                           |           |          |            |              |        |        |        |        |        |                     |
|                             |                                           |           |          |            |              |        |        |        |        |        |                     |
|                             |                                           |           |          |            |              |        |        |        |        |        |                     |
|                             |                                           |           |          |            |              |        |        |        |        |        |                     |
|                             | Sub-total of other contractual:    |           |          |            |              |        |        |        |        |        |                     |
| Total direct costs:  |                                           |           |          |            |              |        |        |        |        |        |                     |
| Total indirect cost: |                                           |           |          |            |              |        |        |        |        |        |                     |
| Total costs:         |                                           |           |          |            |              |        |        |        |        |        |                     |

